### 2.5. Sample Size and Statistical Analyses

In Study 1, since a universe of 137 adoption professionals is available, 57 will need to be recruited in order to achieve a confidence interval of 90%. Study 2 will require a minimum of 171 adoptive parents (95% CI, power of 0.90, medium-to-large effects, multivariate analyses; G*Power [53]). Statistical analyses will be conducted via the Statistical Package for the Social Sciences (IBM SPSS, version 27.0; IBM SPSS, Chicago, IL, USA). Descriptive statistics will be used to explore the adoptive parents’ sociodemographic, clinical, and child characteristics; e-health literacy; needs, preferences, and acceptance regarding *AdoptMindful2Care@Web*; and the adoption professionals’ characteristics and recommendations. Student’s t-test within subjects will be used to analyze the differences between the average number of identified advantages and disadvantages of *AdoptMindful2Care@Web* in both groups and between groups. This same test and chi-square tests will be used to compare other variables between both groups, specifically regarding the perception of usefulness and the acceptability of *AdoptMindful2Care@Web* (in the case of professionals, the report is based on what they perceive to be the opinion of adoptive parents). This comparison will also be conducted concerning the characteristics and functionalities of the platform (e.g., the most useful formats for presenting content) as well as the content itself (e.g., which topics are most relevant and pressing for these parents). These analyses will enable us to determine how the groups differ on these variables. Univariate and multivariate binary logistic regressions will be used to study the associations between independent variables (i.e., sociodemographic and child-related variables, mental health and parenting needs, and e-health literacy) and (1) the perceived utility of and (2) the availability to use *AdoptMindful2Care@Web*. The same will be conducted for adoption professionals to assess the associations between independent variables (i.e., sociodemographic and professional-related data) and the professionals’ (1) perceived utility of *AdoptMindful2Care@Web*, (2) perceptions about the parents’ availability to use *AdoptMindful2Care@Web*, (3) willingness to integrate *AdoptMindful2Care@Web* in their daily work, and (4) willingness to recommend *AdoptMindful2Care@Web* to the adoptive parents with whom they work.

For Study 3, a minimum of 15 individual Think-Aloud Protocol sessions will be held with adoptive parents. Qualitative data will be analyzed by using thematic analysis [54] via the NVivo14© software program. All video and audio recordings of the sessions will be transcribed. On the basis of these transcripts and notes taken during the sessions, usability issues will be identified and rated according to their severity: minor, medium, or critical. Bugs will also be flagged and later reported to web developers. All usability issues rated as medium or critical will be coded on the basis of their content and subsequently mapped according to two predefined categories: navigation or functionality. After this categorization, the categories will be cross-referenced with the general “usability heuristics for users interface design” [55]. These heuristics are often used by experts in the field of user-experience design to inform design decisions, since they offer a set of valuable guidelines developed over decades for designing systems, identifying usability problems and creating better user experiences. The quantitative data will be analyzed via SPSS. Descriptive statistics will be used to explore the perceptions of adoptive parents regarding the prototype version of *AdoptMindful2Care@Web*.

In Study 4, 60 participants (30 per condition; 95% CI, power of 0.99, medium effects, repeated measures ANOVA, and within–between interaction; G*Power [53]) will be needed in the final evaluation. Owing to the expected dropout rate of 60% in e-health interventions [56], we will recruit a total of 96 participants. Statistical analyses will be conducted via IBM SPSS. Descriptive statistics will be used to evaluate the feasibility and acceptability of *Adoptmindful2Care@Web*. Repeated measures ANOVAs/linear mixed models (timeXgroup interaction) will be used to analyze the modifications in participants’ outcomes at the four different assessment times.

In Studies 1, 2, and 4, sociodemographic, clinical, and/or child-related variables will be controlled for in all statistical analyses, in order to account for possible differences between adoptive parents.

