### 2.2. Participants

The participants in Study 1 will be professionals who will have worked in Portuguese adoption services for at least 2 years.

In Studies 2, 3, and 4, the participants will be adoptive parents. To be eligible, parents will have to have (a) at least one adoptive child aged under 18 years; (b) no other adoption process in progress; (c) reading and writing abilities in the Portuguese language; and (d) regular access to the internet and electronic devices. In Studies 3 and 4, parents will be excluded if they will have been diagnosed with a serious mental health condition (e.g., schizophrenia).

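### The t-test named for comparing adoption professionals with adoptive parents is a within-subjects test, but the two survey groups are separate, unlinked people

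*Protocol article*

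**What the plan says.** All the relevant text is in the protocol article, section 2.5 (Sample Size and Statistical Analyses), in the paragraph on Studies 1 and 2.

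- The test is introduced as follows: "Student’s t-test within subjects will be used to analyze the differences between the average number of identified advantages and disadvantages". Its scope is given as "in both groups and between groups".
- It is then carried forward: "This same test and chi-square tests will be used to compare other variables between both groups". The variables named are perceived usefulness and acceptability. The following sentence extends the comparison to platform characteristics and to content.
- The two groups are the Study 1 professionals and the Study 2 parents. A parenthesis explains what the professionals report: "in the case of professionals, the report is based on what they perceive to be the opinion of adoptive parents".
- The purpose is stated as "These analyses will enable us to determine how the groups differ on these variables".
- The planned sizes are "since a universe of 137 adoption professionals is available, 57 will need to be recruited" and "Study 2 will require a minimum of 171 adoptive parents".

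Section 2.2 defines the groups as separate populations. For the first it says "The participants in Study 1 will be professionals who will have worked in Portuguese adoption services for at least 2 years"; Study 2 enrols adoptive parents. Section 2.1 gives each study its own survey. The last paragraph of section 2.5 adds that sociodemographic, clinical and/or child-related variables are controlled for in every analysis of Studies 1, 2 and 4. The article names no independent-samples t-test anywhere.

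**The concern.** A within-subjects t-test needs two measurements on the same unit, or on units linked one to one. Advantages and disadvantages counted by one respondent meet that condition. A professional and a parent do not. Professionals answer partly about how they think parents see the intervention, but this does not link any professional to any particular parent.

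As written, the only t-test available for the professional-versus-parent contrast therefore cannot be applied to the data that will exist. The contrast itself has a purpose: the article says that Phase I findings will inform the content and technical features of the prototype. Whether professionals read parents' views correctly is part of that information. An analyst who follows the text literally would either be unable to run the test or would have to invent pairs, and the answer would then depend on the invention.

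**Working it through.** The article gives no figure for this comparison, so there is none to reproduce. The check has two parts.

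**1. Which comparisons does the named test fit?**

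| Comparison in section 2.5 | Same respondent on both sides? | Within-subjects t-test |
|---|---|---|
| Advantages vs disadvantages, inside the professionals | Yes | Fits |
| Advantages vs disadvantages, inside the parents | Yes | Fits |
| Either count, professionals vs parents | No | Does not fit |
| Usefulness, acceptability, features or content as scores, professionals vs parents | No | Does not fit |
| The same topics as categories, by chi-square, professionals vs parents | Not required | Not involved; chi-square for independent groups is valid |

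Table 1 describes many of the items as multiple-choice or yes/no, with some 5-point Likert items. A good part of the between-group work will therefore fall in the last row.

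**2. What would follow at the planned sizes?**

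Inputs from section 2.5: n1 = 57 professionals and n2 = 171 parents. The latter is a stated minimum, treated here as the actual number. Assumptions, not in the article for this comparison: equal SDs in the two groups, two-sided 5% significance, and standardised differences d from 0.3 to 0.8.

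*Running the named test.* A standard paired t-test routine given 57 and 171 values stops with an error, because there are no pairs.

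*Independent-samples test.*
- SE = √(1/57 + 1/171) = 0.153 SD, with 57 + 171 − 2 = 226 degrees of freedom.
- At d = 0.5 the noncentrality is 0.5/0.153 = 3.27, which gives power of about 0.90.
- Power is about 0.50 at d = 0.3 and above 0.99 at d = 0.8.
- The minimum detectable d is about 0.43 at 80% power and about 0.50 at 90% power.

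*Forced arbitrary pairing, for illustration only.*
- At most 57 parents can be used, so 171 − 57 = 114 are left out (114/171 = 67%).
- Arbitrary pairs carry no correlation on average, so SE = √(2/57) = 0.187 SD.
- The ratio is 0.187/0.153 = √1.5 = 1.22, so the SE is about 22% wider.
- At d = 0.5 the noncentrality is 0.5/0.187 = 2.67 with 56 degrees of freedom, and power is about 0.75.

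*Dependence on the pairing.* One data set was simulated with SD 1 in each group and a true difference of 0.3, and 57 of the 171 parents were paired at random with the professionals 5,000 times. The central 95% of the paired p-values ran from 0.01 to 0.84. The independent-samples test on the same data gives one value, 0.11.

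The unequal sizes make the mismatch visible but are not its cause. With 57 in each group the routine would run, and the pairs would still mean nothing.

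**The case against.** The strongest reply is that this is a misplaced qualifier. The sentence deals with a within-group and a between-group contrast together, and the aim of finding how the groups differ is clear. The phrase about the same test could then simply mean Student's t-test. That reading is plausible. It does not remove the need for a correction, because the within-subjects form is stated explicitly, is applied between groups, and is the only t-test named. Nor is this a detail left to a fuller plan: the article names a test, and for this use it is the wrong one.

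Other points on that side stand, and they limit what a reader might infer:

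- *That every comparison of professionals with parents is invalid.* The article also specifies chi-square tests, which suit independent groups and the many categorical items.
- *That parents will be discarded or that precision will fall by 22%.* Nothing in the article proposes cutting to 57 pairs. A literal attempt at the planned sizes would fail visibly rather than quietly bias a result.
- *That these tests decide what goes into the prototype.* Sections 2.1 and 3 say that Phase I information, taken together, informs it. Needs, preferences and recommendations are mainly summarised descriptively, and no rule ties a design choice to a t-test.
- *That the pilot randomised trial is affected.* Study 4 has its own analysis, and this test plays no part in it.

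**Conclusion.** The point holds in a limited form. For count and continuous variables, the t-test named for professionals against parents does not match the data, because the two groups are independent and unlinked. For advantages against disadvantages within each group the named test is correct. The chi-square comparisons and Study 4 are untouched.

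The finding about the test rests only on the text of sections 2.1, 2.2 and 2.5 and needs no numerical assumption. The 22% wider standard error, the 114 unused parents and the drop in power from about 0.90 to about 0.75 at d = 0.5 illustrate what forced pairing would cost. They are not a forecast of what the investigators will do, and they depend on equal SDs, uncorrelated pairs and exactly 171 parents; the power figures also assume two-sided 5% significance.

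This is a correction worth making in survey work that feeds the prototype. It is not a threat to the trial.

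**What to change.** Reword the two sentences in section 2.5 so that they state:

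1. The paired t-test is used for advantages against disadvantages within professionals and, separately, within parents.
2. Professionals and parents are compared on counts and scores with an independent-samples t-test. Welch's version is a sensible choice given unequal group sizes and possibly unequal variances. The question of whether the balance of advantages over disadvantages differs between groups is answered by computing the within-person difference and comparing it between groups with the same test.
3. Chi-square tests remain for the categorical items.
4. Where the covariate control promised at the end of section 2.5 is meant to apply, the comparison is made with the equivalent linear model: a group term plus covariates measured in both groups. A t-test alone cannot adjust. Table 1 lists sex, age and educational level for both surveys; it lists child-related information for parents and not for professionals, so those variables cannot serve as covariates here.

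The cost is a few lines of text. Neither the questionnaires nor the recruitment targets change, and the planned 57 and 171 already support the corrected comparison at medium differences.

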## Figures and Tables

**Figure 1 healthcare-12-02100-f001:**
[figure not shown]
An overview of the studies included in the protocol.

**Table 1 healthcare-12-02100-t001:** An overview of the variables and anticipated outcomes of the studies and the measurement instruments.

Study	Variables/Outcomes	Measures	
**1** Adoption professionals	**Sociodemographic and Professional** **Information**	**Self-report datasheet, specifically developed by the research team, which will collect information regarding the following:** (1) Sociodemographic data: 3 questions with multiple-choice exclusive answer; e.g., sex, age, and educational level; (2) Professional data: 9 questions with multiple-choice exclusive answer; e.g., position currently held and geographical area of direct activity.	
	**Recommendations regarding *AdoptMindful2Care@Web***	**Self-report datasheet, specifically developed by the research team, which will collect information regarding the characteristics required from *AdoptMindful2Care@Web* to meet the following:** (1) The needs usually expressed by adoptive parents to adoption teams: 4 questions with multiple-choice exclusive answer and multiple-choice questions with several possible answers; e.g., parenting difficulties most commonly reported by adoptive parents to professionals and the moment in which the difficulties are reported to professionals. (2) The adoption professionals’ own difficulties in providing support: 11 questions with multiple-choice exclusive answer, multiple-choice questions with several possible answers, 5-point Likert scale and yes–no answers; e.g., to what extent they think they have enough knowledge and enough time to respond to parents’ requests and level of comfort in providing support to parents in specific areas of difficulty. (3) The ethical and institutional requirements for the integration of the intervention in Portuguese adoption services: 15 questions with multiple-choice exclusive answer, multiple-choice questions with several possible answers, 5-point Likert scale, yes–no answers, and open answers.	
**2** Adoptive parents	**Sociodemographic information**	**Self-report datasheet, specifically developed by the research team:** 15 questions with multiple-choice exclusive answer and open answers; e.g., sex, age, marital status, educational level, professional and socioeconomic status, and number of household members.	

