			**Parents with children > 2 years old** **Interpersonal Mindfulness in Parenting Scale** [IM-P [41]; PV: [43]): self-report measure; 31 items divided into 5 dimensions; Likert scale (ranging from 1 = never to 5 = always); higher scores indicate higher levels of mindful parenting.
	**E-health literacy**	**Portuguese version of the E-Health Literacy Scale** [44]: Self-report measure; 8 items; Likert scale (ranging from 1 = strongly disagree to 5 = strongly agree). Higher scores indicate higher levels of e-health literacy.	
	**Preferences and acceptability of an e-health intervention**	**Self-report datasheet, specifically developed by the research team, which will collect the information regarding the characteristics required of *AdoptMindful2Care@Web* to meet the adoptive parents’ acceptability and preferences regarding the intervention:** 22 questions with multiple-choice exclusive answer, multiple-choice questions with several possible answers, 5-point Likert scale, and yes-no answers; e.g., whether they would find it useful, whether they would be interested in participating, and preferences for content formats.	
**3** Adoptive parents	**Usability of *AdoptMindful2Care@Web***	**The Think-Aloud Protocol** will be used to examine how adoptive parents experience *AdoptMindful2Care@Web* in the context of its actual use. **A self-report datasheet**, specifically developed by the research team, will be used to collect quantitative data regarding the prototype version of *AdoptMindful2Care@Web* (e.g., how appealing and intuitive adoptive parents find the platform).	
**4** Adoptive parents	**Acceptability of *AdoptMindful2Care@Web***	**Self-report datasheet, specifically developed by the project team, which will collect information regarding the satisfaction with the contents and characteristics of the intervention and the opinions regarding the intervention’s quality and relevance:** 25 questions; Likert scale and multiple-choice exclusive answer; e.g., whether taking part in the intervention was useful, whether it helped to improve their relationship with their child, whether they would recommend the intervention to family or friends, whether they consider the technological resources provided by the platform to be adequate, the importance attributed to the different contents covered, and the usefulness attributed to the different technological tools provided.	

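### On yes/no and multiple-choice items, comparing professionals' view of parents with parents' own answers by chi-square can show a difference when nobody misperceives

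*Protocol article*

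**What the plan says.** Section 2.5 (Sample Size and Statistical Analyses) plans comparisons between the professionals of Study 1 and the parents of Study 2. After the t-test on numbers of advantages and disadvantages it continues: "This same test and chi-square tests will be used to compare other variables between both groups", naming usefulness and acceptability in particular. For those it adds that "in the case of professionals, the report is based on what they perceive to be the opinion of adoptive parents". The stated inference is: "These analyses will enable us to determine how the groups differ on these variables".

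In Table 1, the Study 2 parents answer for themselves, for example "whether they would find it useful, whether they would be interested in participating". The formats are mixed on both sides: "22 questions with multiple-choice exclusive answer, multiple-choice questions with several possible answers, 5-point Likert scale, and yes-no answers" for parents, and for the professionals' items on integration into services "15 questions with multiple-choice exclusive answer, multiple-choice questions with several possible answers, 5-point Likert scale", plus yes-no and open answers. One Study 1 item is visibly worded at group level: "parenting difficulties most commonly reported by adoptive parents to professionals". The wording of the professionals' usefulness and acceptability items is not given, and nothing in the article aligns what the two groups are asked about.

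**The concern.** A chi-square test asks whether two response distributions are equal. The parents' distribution reflects how opinion varies from parent to parent. The professionals' distribution reflects how judgements about parents vary from professional to professional. These are different quantities.

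Suppose 65% of parents would use the tool. A well-informed professional who is asked whether parents would use it may simply answer yes. The expected comparison is then 65% against something near 100%, although every professional is right. On such items a rejection does not show misperception, and a non-rejection does not show agreement.

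Section 2.1 says that the prototype is built on the Phase I information. A parent-professional discrepancy that only reflects how the question was put could colour decisions on content, format or dissemination.

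**Working it through.** **Inputs from the article.** Professionals: "57 will need to be recruited in order to achieve a confidence interval of 90" percent, from a universe of 137. Parents: at least 171 (section 2.5).

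**The plan's own figure.** No error rate is stated for this comparison, so there is none to reproduce. The 57 serves here only as an input. With n0 = z² × 0.25 / e² and n = n0 / (1 + (n0 − 1)/137), it corresponds to 95% confidence with a ±10% margin (n0 = 96.04, n = 56.7) or 90% confidence with ±8.35% (n0 = 97.01, n = 57.04). The article gives no margin.

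**Assumptions (not in the article).** A yes/no item; two-sided alpha 0.05; a share p of parents says yes; each professional knows m families and reports their majority view, ties split evenly. Nobody misperceives.

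**Step 1: share of professionals answering yes.** Q = P(X > m/2) + ½ P(X = m/2), with X ~ Binomial(m, p). For p = 0.65 and m = 20, Q = 0.91.

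**Step 2: one typical table.** 52/57 (0.912) against 111/171 (0.649). Pooled share 163/228 = 0.715. SE = √[0.715 × 0.285 × (1/57 + 1/171)] = 0.069. z = 0.263/0.069 = 3.81, so chi-square = 14.5 on 1 df, p = 0.0001.

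**Step 3: rejection rate.** 20,000 simulated surveys per cell, Pearson chi-square without continuity correction:

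| Parents yes | m = 5 | m = 10 | m = 20 | m = 30 |
|---|---|---|---|---|
| 55% | 9% | 15% | 35% | 56% |
| 60% | 19% | 44% | 87% | 98% |
| 65% | 36% | 75% | 99% | 100% |
| 70% | 54% | 92% | 100% | 100% |
| 80% | 78% | 99% | 100% | 100% |
| 90% | 76% | 94% | 96% | 96% |
| 95% | 23% | 24% | 24% | 24% |

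For 60% to 80% yes and 10 to 30 families, the range is 44% to 100%.

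**Step 4: where the effect stops (2,000 runs per scenario).**
- All professionals know p exactly and give the majority answer: 100% rejection for p = 0.55 to 0.80, 96% at 0.90, 24% at 0.95, 0% at 0.98. At p = 0.50 their answers split and rejection is 5%. With 57/57 professionals, significance is lost once parents reach 161/171 (94%; p = 0.062).
- Perception is unbiased but noisy, SD 0.20 on the share: 11% at p = 0.55, 23% at 0.60, 58% to 70% at 0.70 to 0.80, 50% at 0.90.
- Professionals' answers are spread like the parents' own: 3.8% to 5.6% for p = 0.50 to 0.98, about nominal.
- Three-category items with professionals giving the modal answer (parents 40/35/25, 50/30/20 or 70/20/10): 100%.
- Five-point items compared by t-test: at or below nominal if professionals reproduce the parents' mean (Student 0% to 1%, Welch about 5%). If they give the mode or a rounded mean, rejection stays at or below nominal for a symmetric distribution but reaches 45% to 100% (Student) or 88% to 100% (Welch) for the skewed ones tried.

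**Step 5: a like-for-like question.** If professionals report the share of known families who would say yes, its expectation under agreement is p. A simulated Welch-type comparison at p = 0.65 rejected in 5.1% (m = 20) and 5.5% (m = 5). Precision with m = 20: SE = √[0.65 × 0.35/(20 × 57) + 0.65 × 0.35/171] = √(0.00020 + 0.00133) = 0.039, a 95% half-width of about 7.7 percentage points.

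**The case against.** The inflation depends on item wording that the article does not show. The datasheets may ask for a typical parent's rating or already for a share of parents; the binary logistic regressions suggest that utility and availability are analysed as two categories, but not how the question is put. This stands: the size is conditional. A reader might infer that the chi-square will always declare a difference when professionals perceive parents perfectly. The article does not support that, and Step 4 shows where it fails. The numbers of families known also have no source in the article.

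A reader might also infer that every planned test here is invalid. That goes too far: section 2.5 does not assign chi-square to the 5-point items, and a t-test on Likert means need not be inflated.

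Finally, the authors disclose the proxy basis and state no hypothesis about accuracy of perception; they say only that they will learn how the groups differ. As tests of equal responses the tests are valid, and no Phase II decision is tied to a p-value. This limits the harm. What remains is that the text states two different referents, and a difference in responses is then hard to interpret.

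**Conclusion.** The point holds in a limited form. For yes/no and multiple-choice items on usefulness and acceptability, section 2.5 compares a judgement about a group with individual opinions, so the chi-square does not distinguish misperception from accurate perception. If professionals give the majority view, false signals are common over a wide middle range of parent opinion and disappear outside it; if they answer with the parents' spread, there is no problem. It would be wrong to infer that the planned results are bound to be reported as professionals over- or underestimating acceptance, since the article does not say so. The issue is minor: it concerns one exploratory Phase I comparison and does not touch the randomized Study 4.

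**What to change.** For the usefulness and availability items, ask professionals for a number on the parents' scale, for example: out of 10 adoptive parents you work with, how many would find the tool useful, and how many would use it? Report the mean estimate minus the observed parent percentage with a 95% CI (Welch or bootstrap). Add a sentence noting that the parents who respond, being selected by agencies and free to decline, may differ from the families the professionals have in mind; the difference would then mix perception with selection.

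If the surveys are already fielded, show the professionals' proxy answers beside the parents' percentages and drop the significance test for these categorical items, or keep it and state that a significant result is not evidence of misperception.

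Cost: rewording two or three survey items and one analysis sentence, or, after fielding, removing or qualifying one test. Sample sizes and Study 4 stay as they are.

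### Study 1 plans multivariable logistic regression on 57 professionals with 12 candidate items, which puts ordinary odds ratios at serious risk of inflation and separation; Study 2's power statement is not tied to its logistic model

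*Protocol article*

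**What the plan says.** All of this is in the protocol article, section 2.5 and Table 1.

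- **Study 1 size.** The basis is a finite population, "since a universe of 137 adoption professionals is available", of whom "57 will need to be recruited in order to achieve a confidence interval of 90" per cent. No margin of error, power or regression model is mentioned.
- **Study 2 size.** "Study 2 will require a minimum of 171 adoptive parents (95% CI, power of 0.90, medium-to-large effects, multivariate analyses; G*Power [53"]). No test, numeric effect size or number of predictors is given.
- **Model for parents.** "Univariate and multivariate binary logistic regressions will be used to study the associations between independent variables" and two outcomes, perceived utility and availability to use.
- **Model for professionals.** "The same will be conducted for adoption professionals to assess the associations between independent variables (i.e., sociodemographic and professional-related data") and four outcomes: perceived utility, perceived availability of parents, willingness to integrate the tool into daily work, and willingness to recommend it.
- **Items available for Study 1** (Table 1). "Sociodemographic data: 3 questions with multiple-choice exclusive answer" and "Professional data: 9 questions with multiple-choice exclusive answer".
- **Adjustment in Studies 1, 2 and 4.** "sociodemographic, clinical, and/or child-related variables will be controlled for in all statistical analyses".

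**The concern.** The Study 1 sample was chosen to estimate proportions in a small population. The same 57 people are then asked to support four multivariable logistic models. Information in a logistic model is governed by the smaller outcome class, and here that class is small relative to the items on offer. Maximum likelihood then pushes odds ratios away from 1. When nearly everyone answers yes, some coefficients cannot be estimated at all. Questions about usefulness and willingness to recommend may well attract such one-sided answers, although the article gives no expected proportions.

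The stake is moderate. Section 2.1 says the prototype builds on what Phase I finds, so an exaggerated association between a professional characteristic and willingness to use the tool could be read as guidance for dissemination.

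For Study 2, a reader will take 0.90 as the power of the planned association analyses, but the text does not connect the two.

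**Working it through.** **1. What 57 was sized for.** The finite-population formula for a proportion is n = n0 / (1 + (n0 − 1)/137), with n0 = z² × 0.25 / e².
- 95% confidence, e = 0.10: n0 = 96.04, n = 96.04 / 1.694 = 56.7, so 57.
- 90% confidence, e = 0.10: n0 = 67.65, n = 67.65 / 1.487 = 45.5, so 46.

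The number behaves like a survey-precision figure. It matches 95% confidence with a 10-point margin better than 90%, so the wording of the confidence level deserves a check. Either way, no regression model enters.

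**2. Events per predictor, Study 1.** Candidate items: 3 + 9 = 12. All are multiple choice, so an item with more than two categories costs more than one parameter. Events per predictor = N × (smaller outcome share) / 12.

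| N | 50/50 | 70/30 | 80/20 |
|---|---|---|---|
| 57 | 28.5/12 = 2.4 | 17.1/12 = 1.4 | 11.4/12 = 0.95 |
| 137 | 68.5/12 = 5.7 | 41.1/12 = 3.4 | 27.4/12 = 2.3 |

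Ten events per predictor, a common convention, would need 120/0.5 = 240 people at 50/50 and 120/0.2 = 600 at 80/20. Only 137 exist.

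**3. Consequence for the estimates.** Simulation with n = 57, 12 binary predictors, one with a true odds ratio of 2 and the rest null. Odds ratios are averaged on the log scale over fits that converged. The outcome splits are assumptions, since the article gives none.

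| Split | Average of a true OR of 2 | Failed fits | Wald false-positive rate per null predictor |
|---|---|---|---|
| 50/50 | about 2.6 | rare | about 7% |
| 80/20 | about 3.1 | about 6% | about 5.6% |
| 90/10 | not informative | about 54% | falls below 5% among converged fits |

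Repeat runs vary with the definition of a failed fit: about 2.5 to 2.7 at 50/50, about 2.8 to 3.1 with 6% to 9% failures at 80/20, and around half or somewhat more failing at 90/10.

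With Firth's penalty the same true odds ratio averages about 1.9 to 2.1, with almost no failures. With only three predictors and ordinary maximum likelihood it averages about 2.2, with failures of about 1% at 50/50 and 80/20.

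**4. Study 2: can 171 be traced to a model?** Several different calculations at alpha 0.05 and power 0.90 give 171 or very nearly so:
- linear regression, f² = 0.15, 15 predictors: 171;
- linear regression, f² = 0.10, 5 predictors: 171;
- two-group MANOVA, f² = 0.15, 15 outcomes: 171;
- logistic regression, OR 2.0 per SD, prevalence 0.2, R² 0.2: (1.96 + 1.282)² / [0.16 × (ln 2)² × 0.8] = 170.9.

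The source therefore cannot be identified.

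**5. What 171 can detect in a logistic model.** For one standardised predictor, OR = exp{√[(1.96 + 1.282)² / (171 × p(1 − p) × (1 − R²))]}, where R² is that predictor's squared multiple correlation with the others.

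| R² | p = 0.5 | p = 0.8 |
|---|---|---|
| 0 | exp(√(10.51/42.75)) = 1.64 | exp(√(10.51/27.36)) = 1.86 |
| 0.3 | 1.81 | 2.10 |

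**6. Adjustment in all analyses.** Section 2.5 plans descriptive statistics, t-tests and chi-square tests as well as regressions. The first three have no covariate terms, so the promise cannot be kept as worded.

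**The case against.** The strongest reply is that 12 counts questionnaire items, not model terms. Section 2.5 names two domains of predictors and does not say that every item enters one model. Running univariate models alongside multivariable ones is compatible with screening first, and selection rules may sit in a fuller plan that is not shown. This stands: the models are at risk if the items enter, and it would be wrong to say they will be overfitted. With three predictors the problem largely disappears at 50/50 and 80/20.

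A second reply is that 57 is the number needed, not a ceiling. That does not rescue the full model, because even all 137 professionals give at most 5.7 events per item.

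A third is that these are formative surveys, reported mainly by descriptive statistics. This also stands and limits the importance of the point.

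Three stronger readings are tempting and are not supported:
- **171 came from a linear-regression calculation.** The exact match at 15 predictors invites this, but other inputs, including logistic ones, match as well.
- **The 0.90 power does not apply.** It is unverifiable from the text rather than shown to be wrong, and it is claimed for Study 2 only, never for the professionals' models.
- **False positives are the main harm, or Study 2 is equally affected.** The Wald error rate rises only to about 7%. With 171 people and 15 independent predictors, a true odds ratio of 2 averages about 2.2 with no failed fits, so the bias there is modest.

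**Conclusion.** The point holds for Study 1 in conditional form. A sample sized for survey precision is assigned multivariable logistic models for which 12 candidate items are documented. If those items enter, ordinary odds ratios are seriously exaggerated (2 becomes roughly 2.6 to 3.1), and fits fail often when answers are very one-sided. These sizes rest on assumed outcome splits and on binary, mutually independent predictors; items with more categories would make matters worse.

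For Study 2 the finding is narrower: the sample-size statement does not name the model it serves, so its power claim cannot be checked against the planned logistic regression. The adjustment sentence is a small wording error. None of this concerns the pilot trial's sample size or its time-by-group comparison.

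**What to change.** In section 2.5:

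- **Study 1.** State that the professionals' multivariable models will use Firth-penalised logistic regression, or that each will contain no more than two or three pre-named predictors, and label them exploratory. Firth estimation is the safer choice if answers are very one-sided: at 90/10 even three predictors leave 57 × 0.1 / 3 = 1.9 events each.
- **Study 2 (optional).** Name the test, effect size and number of predictors behind 171, or add the odds ratio detectable with 0.90 power: about 1.64 to 1.86 per SD for one uncorrelated predictor, and 1.81 to 2.10 with R² 0.3, for outcome splits from 50/50 to 80/20.
- **Adjustment.** Limit the sentence on controlling for covariates to the model-based analyses.

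The cost is wording, plus either fewer simultaneous predictors or a small extra software step. The power statement for Study 2 may look less favourable. No change in recruitment is needed.
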